#### Measures and Data Collection Procedures

Data from each IETP participant will be obtained from site leads beginning with Tampa (2015 to present; n=approximately 350). We will obtain identifiers that allow linkage to VA and DoD health system data and create a study crosswalk database behind the VA firewall that includes the encrypted identifier, a study ID, and contact information for interview and survey administration. We will obtain intake and discharge measures from each IETP site. We will assess IETP fidelity based on the IETP characterization table (Multimedia Appendix 1) using a checklist (Multimedia Appendix 2) and chart abstraction focusing on the admission note, admission IETP care plan, discharge TBI care plan, and discharge summary, which are highly accurate in describing the reasons for seeking treatment, baseline status, the type of treatment recommended, the type of treatment received, and outcomes on discharge (Multimedia Appendix 12).

We will also link these IETP data to VA and DoD health system data, as we have done previously [36], to obtain information on physical and mental health, medications, and military demographic data before and after IETP. As approximately 90% (225/250) of participants in the IETP are active duty at the time of treatment with the goal of returning to full duty and operational partner priority outcomes include return to duty or employment, the use of VHA data (eg, Patient Health Questionnaire-9 [PHQ-9] and PTSD checklist-5) is not a feasible approach to long-term outcomes. Therefore, we will conduct a survey using a VA-approved web-based survey software for participants of IETP (2015-2022; approximately 500) using a Modified Dillman Method, which we used in prior VA studies (Multimedia Appendix 13) [37-40]. We will begin a survey of earlier IETP graduates in the first year of the study and send surveys to new graduates 6-9 months post study completion. The final outcome measures included in the survey will be developed in collaboration with stakeholders. The current list of stakeholder-identified measures that are evaluated at intake and discharge include the PHQ-9, PTSD checklist-5, MPAI, and the Neurobehavioral Symptom Inventory.

We will also use VA and DoD health system data to describe health system outcomes such as use, new diagnoses, and adverse outcomes, which will, together with data baseline, discharge, fidelity, and discharge outcomes, be used to develop trajectories of recovery.

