#### Characterize IETP Participants

We will begin characterization with the Tampa site (n=approximately 350) and Richmond site (n=approximately 150), followed by other sites. We will use VA and DoD health system data to characterize preadmission military and sociodemographic characteristics, TBI-related diagnoses (eg, PTSD, pain, and sleep), and medication use (eg, opioids, antidepressants, and sedative hypnotics). We will add data from TBI history and symptom inventories administered at IETP admission to develop mild TBI phenotypes [36,41,42]. This allows the characterization of participants in the IETP and the identification of groups that are likely to have similar courses of care.

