#### Data Analysis

After calculating descriptive statistics (proportions and quantiles for discrete variables and means and SDs for continuous variables) of VHA and DoD intake measures before IETP admission, we will fit a latent variable mixture model, a multivariate statistical technique used to classify individuals into interpretable categories based on a set of measurements (described in the *Measures and Data Collection Procedures* section) [36,42-49]. Similar to cluster analyses, the latent variable mixture model is an exploratory technique to identify underlying constructs associated with multiple variables, in our case, the underlying comorbidity phenotypes. On the basis of prior work, we expect 2 to 3 groups each with n=approximately 100-200 participants [36]. Health system data identifying the treatment provided are not likely to have missing data owing to the professional responsibility to document. Each visit requires a primary diagnosis for care, which will lead to data available at each visit; therefore, we expect little to no missing data.

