#### Identify Treatment Received During IETP

Consistent with prior studies [50-52], we will create an abstraction tool in collaboration with IETP clinicians and aim 1 data. Using the crosswalk database, we will conduct chart abstraction for IETP focusing on the initial assessment, TBI care plan, processes and amount of care received, discharge assessment, and TBI care plan. After finalizing the procedures and appropriate training, team members will independently review 10 charts and then meet to identify inconsistencies, errors, or disagreements and resolve any by consensus. This will continue until there is 90% agreement on all items abstracted, to ensure abstraction fidelity. The areas of uncertainty will be discussed with IETP clinicians. These data will be merged with IETP data, VA and DoD analytic file data, and survey data for the outcome analyses.

We will identify what happens during the IETP stay using descriptive statistics for the overall cohort, stratified by phenotypes from the measures listed in the *Measures and Data Collection Procedures* section. We expect that different types of care will be provided to individuals with different prior comorbidities and clinical presentations. We will apply Pearson chi-square test to assess the association between recommendations for admission TBI care plan and TBI phenotype.

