#### Identify Components of IETP Associated With Sustainment and Improvement Trajectories

Outcomes currently identified by operational and clinical stakeholders that are collected at all sites (Tables 3 and 4) will be included in the survey to develop longitudinal outcome trajectories. On the basis of stakeholder feedback, we will also measure and describe community reintegration, employment, retention in the military where relevant, compliance to discharge from the TBI care plan, reasons for difficulty in care plan compliance, and unmet rehabilitation needs. Per operational partners’ request, we will also use VHA and DoD data to identify use relevant to discharge (eg, TBI care plan within primary, mental health, specialty care, or emergency care).

We will use Bayesian network analysis to generate a directed acyclic graph, which probabilistically describes the trajectory of symptoms, care, and outcomes for IETP participants. This network will enable us to explore the contribution of the baseline phenotype to the decision to use a particular treatment course and the contribution of those treatments to the participants’ resulting outcome measures [53]. Using a hill-climbing algorithm scored with the Bayesian information criterion, we will establish directional connections between nodes, called edges, and evaluate the robustness of the edges using bootstrapped samples of the data. We will a priori exclude any implausible directed edges (eg, IETP care cannot lead to precare symptoms). The resulting directed network will have edges between the levels: (1) phenotypes, (2) treatment, and (3) outcomes, while disallowing connections that go from levels 2 to 1 or 3 to 2 or 1. We can allow edges between nodes within the treatment level of the network to better understand the interactions between treatments and to assess how the treatments individually and in combination probabilistically affect patient outcomes. By fitting this model, we can isolate the most probable trajectories between TBI phenotypes and treatments and then determine which treatments have a higher probability of positive long-term outcomes. To gain an understanding of the treatment courses on outcomes, we will present a graphical display of the nodes and edges, the conditional probabilities calculated between nodes that estimate the probability of long-term outcomes given the participants’ IETP components and comorbidity phenotypes, and the robustness measures from bootstrapping.

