#### Power and Missing Data

The analyses in this aim take an exploratory approach to establishing phenotypes with latent variable mixture models and isolating common trajectories based on Bayesian networks. As such, we do not have a targeted hypothesis with which to power this analysis for minimum detectable effect sizes but rather a model selection approach using the Bayesian information criterion. With 500 participants, we expect that our sample size will be well above the number of nodes in the Bayesian network, which will allow for an accurate estimation of the conditional probabilities in the network [54,55].

We will assess the risk of bias owing to missing data by looking at patterns of missing measurements at each phase of the patients’ trajectories, although we expect most missingness to be postdischarge. Reasons for missing measurements will be tabulated with a focus on differentiating missed measurements for logistical reasons from dropouts or intermittent missingness potentially related to the condition of the patient. If >10% (25/250) of the patients have missing outcome measurements for any of the follow-up measures or if the comparisons of baseline characteristics between patients with missing and nonmissing measurements indicate considerable imbalances, rather than only looking at complete cases, we will apply the structural expectation-maximization algorithm, an imputation method that directly processes data with missing values while fitting the Bayesian network [56]. This method incorporates baseline and follow-up factors beyond the variable being analyzed to account for the dependence of missing data on other factors. TBI history is a primary piece of data required for admission to the program. It is unlikely that any data will be missing for TBI history. However, if >20% (>50/250) of the sample has missing data related to TBI history, the study should be stopped.

### Aim 3

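### A phenotype of 2 to 3 expected classes is the only named pre-treatment level in the Bayesian network, so severity differences within a class may bias the component–outcome edges

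*Protocol article*

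**What the plan says.** The aim 2 section on components associated with trajectories defines the network by level: "The resulting directed network will have edges between the levels: (1) phenotypes, (2) treatment, and (3) outcomes". It bars edges that run backwards through these levels. The reported conditional probabilities are those that "estimate the probability of long-term outcomes given the participants’ IETP components and comorbidity phenotypes". Neither sentence names an intake score.

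On the phenotype, the aim 2 Data Analysis section says "we expect 2 to 3 groups each with n=approximately 100-200 participants". Its inputs include admission data: "We will add data from TBI history and symptom inventories administered at IETP admission to develop mild TBI phenotypes".

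The outcome measures are already scored before treatment. The aim 2 Measures and Data Collection Procedures section says the stakeholder-identified "measures that are evaluated at intake and discharge include the PHQ-9, PTSD checklist-5, MPAI, and the Neurobehavioral Symptom Inventory", and Table 3 ticks baseline, discharge and survey for all four.

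On who gets which care, the section on treatment received says: "We expect that different types of care will be provided to individuals with different prior comorbidities and clinical presentations".

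On sample size, Power and Missing Data says "With 500 participants, we expect that our sample size will be well above the number of nodes in the Bayesian network". It calls the analysis exploratory and gives no effect size.

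**The concern.** If care follows presentation, sicker patients receive different components, and sicker patients also tend to score worse later. That is confounding by indication. The strongest single confounder of a survey score is usually the same patient's intake score on that measure. The plan has that score in hand, but the stated conditioning set replaces it with a class that has 2 or 3 values. Patients within one class can still differ in severity, and any such difference that also steers treatment passes into the component–outcome edge.

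This matters because the network is meant to show which treatments more often lead to good long-term outcomes. The Preimplementation Stage, Principal Findings and Conclusions sections carry the findings into withdrawal of components judged ineffective. Potential Limitations confirms that there is no comparison group, so covariate adjustment is the main protection. The bootstrap check on edges does not help here: it measures sampling stability, and a confounded edge can be stable.

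**Working it through.** The plan states no figure on this point, so there is none to reproduce. The check asks how much a component with zero true effect would appear to do.

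**Inputs from the article:** three levels; 2 to 3 classes; n=500; edges scored by the Bayesian information criterion (BIC).

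**Assumed inputs (not in the article):** standard normal intake severity S, higher is worse; correlation of S with the follow-up score ρ=0.6; odds of receiving the component rise 1.5 or 2 times per SD of S; phenotype is three equal classes cut from an index sharing R²=0.3 or 0.6 of its variance with S.

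**Step 1: severity left inside a class.** Cutting a normal variable into three equal classes captures 0.793 of its variance (two classes: 2/π = 0.637). The share of severity variance left within a class is V = 1 − 0.793·R² for three classes.
- If class were purely severity: 1 − 0.793 = 21% (two classes: 36%).
- At a class–severity correlation of 0.5 (R²=0.25): 1 − 0.793·0.25 = 80% (two classes: 84%).

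**Step 2: spurious effect on a follow-up score.** To first order, treated and untreated patients in a class differ in severity by ln(OR)·V, so the bias is about ρ·ln(OR)·V. The formula runs slightly high at larger odds ratios. The simulation used 1,000 data sets per setting and added an edge if n·ln(RSS0/RSS1) > ln n.

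| R² | OR | V | 0.6·ln(OR)·V | Simulated bias (SD) | False edge, n=500 | False edge, n=250 |
|---|---|---|---|---|---|---|
| 0.3 | 1.5 | 0.762 | 0.185 | 0.18 | 35% | 20% |
| 0.3 | 2 | 0.762 | 0.317 | 0.29 | 82% | 52% |
| 0.6 | 1.5 | 0.524 | 0.127 | 0.13 | 18% | 10% |
| 0.6 | 2 | 0.524 | 0.218 | 0.20 | 46% | 26% |

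**Step 3: hand check of the false-edge rate.** At n=500 the BIC rule needs |z| above √(ln 500) = √6.21 = 2.49. For R²=0.3 the residual variance given class is 1 − 0.36·0.238 = 0.914, so the standard error is about √(0.914/(500·0.25)) = 0.0855. A bias of 0.18 gives z = 2.11 and P(Z > 0.38) = 35%. A bias of 0.29 gives z = 3.39 and P(Z > −0.90) = 82%. Both match the table.

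**Step 4: with the intake score added.** Bias is about 0 and false edges fall to 1–2%, as expected from P(|Z| > 2.49) = 1.3%. The zero bias is partly by construction: in the simulation the intake score is the only confounder and has no measurement error.

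**Step 5: outcome as change from intake.** The bias becomes (ρ − 1)·ln(OR)·V. With R²=0.3 and OR=2 it is −0.4·0.693·0.762 = −0.21, so a null component looks helpful. Over a wider grid (two or three classes, ρ 0.5–0.7, log-odds 0.5–1.0 per SD, class–severity correlation 0.5–1.0) the false benefit runs from 0.03 to 0.35 SD. On that grid the false harm on a follow-up score runs from 0.05 to 0.50 SD.

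**Step 6: discrete network.** The article reports conditional probabilities between nodes, which may mean categorical nodes. With the Step 2 settings, the outcome in 2 or 3 categories and BIC-best parents, false edges at n=500 occur in about 0–21% of samples. Adding an intake node cuts this to under 1%. A truly helpful component (−0.3 SD) is kept in 0–8% of samples when only the intake edge is forced, against roughly 0–1% under the plan. If the full component-by-phenotype-by-intake table is forced, it is kept in 0%.

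**The case against.** Four objections carry weight.

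- **Severity is not ignored.** A reader might infer that the plan makes no adjustment for it. The article does not support that: admission symptom inventories, diagnoses and medications feed the phenotype. If the classes were cut from severity itself, the bias would fall to 0.05–0.08 SD and false edges at n=500 to 3–6% in the linear case. But nothing in the plan ensures that a comorbidity phenotype tracks severity that closely.
- **Intake scores may be nodes.** A reader might take their exclusion as settled. It is not: the article gives levels, not a node list, and its example of a barred edge is "IETP care cannot lead to precare symptoms", which suggests that precare symptoms could be nodes. The imputation method is also said to draw on baseline factors. Still, no listed level holds those symptoms apart from the phenotype, and the conditioning sentence leaves them out.
- **The direction is not fixed.** A reader might infer that components for sicker patients will look harmful. That requires a follow-up-score outcome and sicker patients within a class receiving more of the component. The section heading and Table 3 speak of trajectories that include baseline; if the outcome node is change, the bias reverses.
- **The consequence is indirect.** The analysis is labelled exploratory, and aim 3 triangulates it with qualitative findings and stakeholder review. An edge alone withdraws nothing. Deimplementation nevertheless remains a stated goal that these results inform.

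The percentages depend on assumed inputs and on network type, and the bootstrap step was not simulated.

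**Conclusion.** The concern holds in limited form. As written, adjustment for pre-treatment severity runs through a coarse phenotype, and the reported outcome probabilities do not condition on intake scores that are already collected. Severity differences within a class may therefore distort component–outcome edges, in a direction that depends on how the outcome node is defined.

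Under the assumed inputs, the spurious effect on a follow-up score is about 0.13 to 0.29 SD. False edges at n=500 occur in about 18–82% of samples for a linear network and about 0–21% for a discrete one. These figures illustrate the problem and do not predict this study's results, since the article gives none of the three driving quantities. In both network types, adding the intake score brought false edges down to 2% or less and did not worsen detection of a helpful component, provided the full cross-table was not forced. The point should be settled before the network is fitted.

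**What to change.** 1. State whether the intake scores are nodes. Add the intake score of each Table 3 measure to level 1, as a parent of the matching follow-up outcome node and a permitted parent of treatment nodes.
2. Define the outcome node as the follow-up score given the intake score, not raw change.
3. Report component–outcome results with and without the intake scores, so that readers can see how far each edge depends on them.

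No new data collection is needed. The cost is extra parameters. In a discrete network these make the conditional probability tables sparser: one two-level component by three phenotypes has 6 cells, about 83 patients each at n=500, while adding an intake score in thirds gives 18 cells, about 28 each. Intake scores should therefore be kept in few categories, and the full component-by-phenotype-by-intake table should not be forced.

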#### Preimplementation Stage: Data to Knowledge

Aim 1 qualitative methods will fully characterize the successful IETP model and the perceived value of IETP components. We will leverage existing data resources and prospective data collection to evaluate program outcomes prioritized by our operational partner and other stakeholders, including service members and veterans with mild TBI (aim 2). Findings from the first 2 study aims will be used to develop the foundation for the implementation of effective components and the deimplementation of ineffective components in aim 3.

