#### Overview

In aim 3, aim 1 and aim 2 data will be triangulated to develop a final report to support IETP full implementation at sites. The primary deliverable for aim 3 is a final report that will include the IETP characterization table, IETP Care Implementation Elements Inventory, IRLM, patient experience data summaries, implementation checklists, educational content, and templates. A concluding presentation will be delivered, and consultation on findings integration will be provided for each site. In year 3, we will conduct site visits and presentations with each program to present the developed content and consult with each site to individualize and prioritize how content can be tailored at each site to facilitate full IETP implementation, including the deimplementation of ineffective care.

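### Aim 2's BIC-scored network cannot tell a component with no benefit from one whose benefit was not detected, yet its results inform which components are called ineffective

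*Protocol article*

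**What the plan says.** In the Aim 2 section on components associated with sustainment and improvement trajectories, the network is learned as follows: "Using a hill-climbing algorithm scored with the Bayesian information criterion". Edges are checked on bootstrap samples, and the fitted network is then used to "determine which treatments have a higher probability of positive long-term outcomes". The outputs named are the graph, conditional probabilities of long-term outcome given components and phenotype, and the bootstrap robustness measures.

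Under Power and Missing Data the analysis is called exploratory: "we do not have a targeted hypothesis with which to power this analysis for minimum detectable effect sizes". The sample size is supported only by comparison with the size of the network: "With 500 participants, we expect that our sample size will be well above the number of nodes in the Bayesian network".

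The use of the results is stated more firmly. The section Preimplementation Stage: Data to Knowledge makes the findings of Aims 1 and 2 the basis for "the implementation of effective components and the deimplementation of ineffective components in aim 3". The Aim 3 Overview describes site consultation "to facilitate full IETP implementation, including the deimplementation of ineffective care". The overview of the QUERI Implementation Roadmap section and the Conclusions say the same in substance. The article does not define an ineffective component.

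**The concern.** A network selected by BIC is built to be sparse: an edge enters only if it pays for its parameters. An edge that enters is some evidence of association. An edge that stays out may mean that there is no effect, or that a real effect was too small for the penalty at this sample size. The article puts both kinds of finding to use, effective components for implementation and ineffective ones for deimplementation, but gives no way of telling those two meanings apart.

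The planned outputs could hide the difference:

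- **Conditional probabilities.** If a component is connected to an outcome only through phenotype, the fitted network gives it a difference of exactly zero within phenotype. The display would then show no effect, with no uncertainty attached.
- **Bootstrap.** Each resample is scored with the same penalty. The result is how often an edge is selected, not an interval for the size of an effect.

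At stake is that a component with a modest real benefit is presented to sites as a candidate for removal.

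**Working it through.** The article states no power or detectable effect, so there is no figure of that kind to reproduce. The 500 matches the two site counts in Characterize IETP Participants, about 350 + about 150 = 500.

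**Inputs from the article.** n = 500. As a lower scenario, n = 250, the denominator used in the same section for missing data ("If >10% (25/250) of the patients have missing outcome measurements for any of the follow-up measures"). Two to three phenotype groups, taken here as three. BIC scoring.

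**Inputs assumed, because the article gives none.** A binary outcome and a binary component; three equally common phenotypes with good-outcome rates of 40%, 50% and 60% without the component; a benefit of 10, 15 or 20 points in every phenotype; uptake of 50% or 85%, unrelated to phenotype.

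**Step 1: the threshold for an edge.** BIC adds an edge when the likelihood-ratio chi-square exceeds df × ln(n).

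- No other parent of the outcome, df = 1: ln(500) = 6.21, equivalent to p = 0.013; ln(250) = 5.52, p = 0.019.
- Three-class phenotype already a parent: parameters go from 3 to 6, so df = 3. 3 × ln(500) = 18.64, p = 0.0003; 3 × ln(250) = 16.56, p = 0.0009.
- With a two-class phenotype as parent, df = 2: 2 × ln(500) = 12.43, p = 0.002.

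**Step 2: how often a true effect is kept.** The search must also decide whether phenotype becomes a parent of the outcome, so the relevant rate comes from running the greedy search over both. Simulated rates at which the component's edge is kept:

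| True benefit | n=500, 50% uptake | n=500, 85% uptake | n=250, 50% uptake | n=250, 85% uptake |
|---|---|---|---|---|
| 10 points | 23% | 10% | 20% | 10% |
| 15 points | 61% | 30% | 44% | 22% |
| 20 points | 88% | 55% | 73% | 40% |

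Repeat runs agree to within about 3 points.

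**Step 3: the two conditional cases.** At n = 500 and 50% uptake, if phenotype is taken as already a parent, a 10-point benefit is kept in about 4% of samples and a 15-point benefit in about 26%. With no other parent in play, the rates are about 40% and 81%. The full search lies between these.

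**Step 4: what an interval would show.** The approximate 95% half-width for a risk difference, with outcome rates near 50% and uptake u, is 1.96 × √[0.25/(n·u) + 0.25/(n·(1−u))].

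- n = 500: 8.8 points at u = 0.5, 12.3 points at u = 0.85.
- n = 250: 12.4 and 17.4 points.

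Suppose, for illustration, that 10 points were the smallest worthwhile benefit. At n = 500 and 50% uptake, an interval lies wholly below it only if the estimate is under 10 − 8.8 = 1.2 points. At 85% uptake the estimate must be under 10 − 12.3 = −2.3 points, that is, in the wrong direction. In most settings the data could seldom show that a component lacks a 10-point benefit.

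**The case against.** A reader might infer that the plan labels every component without an edge ineffective and removes it. The article does not say so. It uses the network in the positive direction, to find components associated with better outcomes, and a condensed article may leave a definition of ineffective to a fuller document. The route to deimplementation is also not automatic. Aim 1 data are triangulated with Aim 2, the stakeholder panel reviews and validates content, each site is consulted individually, and the section on sustainment leaves deimplementation and its effects to future work. The limits of the design (exploratory, no comparison group) are disclosed. All of this stands, and it lowers the severity.

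A reader might also infer that the network will usually miss any useful component. That is too strong. At n = 500 and 50% uptake, 15-point and 20-point benefits are kept in most samples. Rates as low as 4% and 26% apply only when phenotype is already a parent of the outcome, which the search does not guarantee.

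It is fair, too, that the binary nodes are an assumption: the listed outcomes are scale scores. For a continuous outcome at n = 500, 50% uptake and no other parent, 80% detection needs a standardised difference of 0.30; with a three-class phenotype as parent it needs 0.45. The pattern is the same.

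What the objection does not answer is that conditional probabilities and bootstrap edge frequencies, as described, give no measure of uncertainty for a component whose edge was dropped. Aim 1 is qualitative and supplies no effect estimate either.

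**Conclusion.** The concern holds in a limited form. The article commits to identifying ineffective components, while its only quantitative component-outcome analysis cannot separate no benefit from benefit not detected. Nothing in the planned outputs prevents a missing edge from being read as ineffectiveness, although the article does not itself make that reading.

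Under the stated assumptions, a benefit of about 10 points is missed in most samples in every scenario examined. A 15-point benefit is missed in most samples at 85% uptake or at n = 250. At n = 500 a 20-point benefit is missed in about 12% of samples at 50% uptake and 45% at 85%. These rates depend on assumed effect sizes, uptake, outcome type and phenotype prevalence. Survey non-response, for which the article gives no rate, would lower detection further.

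This is a worthwhile and inexpensive improvement, not a condition for the evaluation to proceed.

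**What to change.** 1. For every abstracted component, whether or not its edge is kept, report the phenotype-adjusted outcome difference with a bootstrap interval.
2. State in the Aim 2 and Aim 3 text that absence of an edge is not evidence of ineffectiveness.
3. Set a minimum worthwhile benefit with the stakeholder panel before the outcome analysis. Describe a component as having little or no benefit only when its whole interval lies below that value. Where the interval neither excludes that value nor supports a benefit, call the component inconclusive.

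The cost is a little more analysis on data already being collected, some wording, and one panel decision. The drawback is that fewer components can be called ineffective; step 4 of the working suggests that few will qualify when uptake is high.
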